### Pharmacodynamic (PD) data analysis

The serum cortisol and salivary glucocorticoid results will be used to estimate the total cortisol exposure, the peak cortisol response and the time of this response. The paired serum and salivary cortisol, and serum cortisol and salivary cortisone concentrations will be analysed for correlation to ensure accurate generation of the total cortisol exposure data. This PD data analysis requires a minimum of 12 participants to produce adequate samples (37.5% of the final sample size).

### Patient and public involvement and engagement

The initial study design phase included consultation with the Lay ADvice on Diabetes and Endocrine Research (LADDER) group at Sheffield Teaching Hospitals NHS Foundation Trust and patient and public involvement and engagement (PPIE) groups at Sheffield Children’s NHS Foundation Trust, specifically convening cohorts of adults and paediatric patients (and their parents) with experience of the SST and salivary tests in order to better understand the unmet needs. Their input into research design, delivery and dissemination plans, and in planning ongoing PPIE activities was also sought.

Further meetings with the LADDER group and additional Sheffield Children’s Hospital PPIE groups have been used to facilitate the codesign of trial documentation, and their input will be sought later in the study to assist with dissemination plans.

Additionally, two PPIE representatives have been identified as members of the independent Trial Steering Committee to assist with study oversight.

## Ethics and dissemination

### Regulatory approvals and trial oversight

The trial protocol and amendments have been reviewed and approved by the South Central–Hampshire A Research Ethics Committee (23/SC/0073) and by the MHRA. Sheffield Children’s NHS Foundation Trust is the study sponsor, and HHTU is responsible for trial implementation and management.

A Trial Management Group has been convened to oversee trial delivery and operations. An independent Trial Steering Committee will provide overall trial supervision on behalf of the study sponsor and project funder. A Data Monitoring and Ethics Committee (DMEC) will monitor progress, review efficacy and safety data and make recommendations on study conduct and continuation, where necessary.

### Safety considerations and AE reporting

Participants will be monitored especially closely for any hypersensitivity reaction during the first 30 min after IMP administration, and then throughout the rest of their study visit. Symptoms associated with the nasal drug administration will not be reported as AEs, unless persistent (defined as still present 30 min after IMP administration). Any AEs will be reported electronically via the study database.

The occurrence of one possibly related SAE or two possibly related severe AEs will trigger trial stopping criteria. The trial can only be restarted following discussion with the DMEC and MHRA approval of a substantial amendment.

If a possibly related SAE or severe AE occurs in an individual participant, they should not receive any subsequent IMP doses and will be withdrawn from the trial.

Emergency unblinding is available 24/7 in the event of a medical emergency.

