## Introduction

 Adrenal insufficiency (AI) describes the inability of the adrenal glands to produce an adequate amount of the essential stress hormone, cortisol. AI is classified as either primary (adrenal), secondary (pituitary) or tertiary (hypothalamic, mainly adrenal suppression secondary to prolonged, high-dose exogenous steroid use), dependent on its origin.^1^

Diagnosis of AI is often delayed, due to presentation with non-specific symptoms, leading to an increased risk it will manifest as an episode of adrenal crisis, which carries an associated 6% mortality rate.^2^ The most commonly used and recommended test for diagnosing AI in current clinical practice is the Short Synacthen Test (SST).^3^,^5^ The SST involves either intravenous or intramuscular injection of Synacthen (tetracosactide), a synthetic analogue of adrenocorticotropic hormone (ACTH), consisting of the N-terminal 24 amino acids (1–24), followed by blood sampling at 30±60 min to quantify the serum cortisol response. Requests for SSTs are increasing across all healthcare sectors,^5 6^ likely due to rising concerns around the iatrogenic nature of tertiary AI and increased prescription of glucocorticoid therapies that suppress adrenal function. However, the test is time, labour and resource intensive, requiring skilled personnel and a medical day care admission. It also requires cannulation (or administration of intramuscular Synacthen) and venous sampling, which may be distressing and painful, especially for children. There is an unmet need for a less invasive, less resource-intensive and therefore more cost-effective test to diagnose AI.

Intranasal administration is a minimally invasive technique that can be used to effectively deliver drugs, with the advantages of avoidance of first pass metabolism, good absorption due to the richly vascular nasal mucosa and a rapid onset of action.^7^ Furthermore, minimal training is required to administer the drugs and use of needles can be avoided. Current evidence suggests that the side effects of nasal drugs are few, generally attributable to the drug itself rather than the method of delivery, and resolve rapidly.

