The Nasacthin test, which uses an intranasal formulation of tetracosactide (the active pharmaceutical ingredient (API) in Synacthen), has been developed to address this unmet need. Within the Nasacthin formulation, tetracosactide is coupled with chitosan, a mucoadhesive agent, in order to aid nasal absorption. This can be administered nasally via a spray, with the resultant glucocorticoid levels measured in saliva samples to quantify the adrenal response.

Salivary glucocorticoid estimation is growing in popularity due to the advantages of non-invasive sampling and close correlation between salivary cortisol and cortisone, and biologically active free serum cortisol. Salivary cortisol is a validated, well-established alternative to invasive glucocorticoid sampling, and is recommended as a first-line diagnostic test for Cushing’s syndrome.^8^ It has also been investigated following Synacthen stimulation in healthy volunteers and patient populations,^9 10^ and specifically following Nasacthin administration in healthy adult males and children.^11^ However, it is salivary cortisone that has emerged as the preferred salivary biomarker as, due to rapid metabolism of salivary cortisol to cortisone, it is the more abundant glucocorticoid and gives a closer reflection of serum cortisol levels, with better sensitivity at low serum cortisol levels.^10 12 13^ A recent prospective diagnostic accuracy study showed that the waking salivary cortisone level was a strong predictor of the serum cortisol response to Synacthen in the SST.^14^

To date, four pharmacokinetic-pharmacodynamic studies (PK-PD)and a reproducibility study have been completed,^11^ in which a total of 70 doses of Nasacthin have been administered to healthy adult males and children. All participants were dexamethasone suppressed to allow quantification of ACTH_(1–24)_ for PK analysis. These studies found Nasacthin to be reliably absorbed and well tolerated, and importantly demonstrated a comparable plasma cortisol response to the intravenous Synacthen test, and that 60 min is the optimal timing of salivary glucocorticoid sampling following Nasacthin.^9^

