### Study aims and objectives

The STARLIT-2 study primarily aims to demonstrate non-inferiority in serum cortisol response following administration of nasal tetracosactide (Nasacthin) to the response following intravenous tetracosactide (Synacthen) administration. In addition, the study will seek to confirm the superiority of active treatments (Nasacthin and Synacthen) over their respective placebo comparators.

As secondary objectives, the study will examine the salivary cortisone response following Nasacthin stimulation with the aim to demonstrate that this is non-inferior to the response following adrenal stimulation with Synacthen, as well as looking at the non-inferiority of the serum cortisol response using change from baseline values instead of absolute values. The study will collect safety data on the use of Nasacthin in healthy volunteers, and will explore the acceptability, usability and tolerability of the Nasacthin test to participants and healthcare professionals. A further exploratory objective will compare the serum cortisol, salivary cortisol and salivary cortisone response at 30 and 60 min after drug administration to explore the relationship of the glucocorticoids in the dynamic phase following administration.

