The NPA, defined as the proportion of participants for which the Nasacthin test produces a rise above a predefined threshold (430 nmol/L) in serum cortisol at 30 min, using response to Synacthen as the reference standard, will be compared with 77.5% using a one-sided exact test, and an exact CI will also be provided. The significance level (alpha) used for the test has been nominally set at 0.025, but again will be determined by the results of the tests of the superiority primary objectives.

The secondary objectives to demonstrate non-inferiority in serum cortisol and salivary cortisone levels between 500 µg Nasacthin and 250 µg Synacthen will use the same methodology as the primary non-inferiority objective; however, they will use the 60 min timepoint and, for salivary cortisone, the non-inferiority margin will be set at ±25 nmol/L. Again, this non-inferiority margin is based on the published repeatability coefficient of previous work,^11^ with adjustment for the lack of dexamethasone suppression.

For the safety analysis, all participant visits in which Nasacthin (active) was administered will be included in the analysis. Any AEs reported in association with administration of placebo or Synacthen will be summarised as a comparison. AEs, SAEs and SUSARs will be summarised by treatment received, system organ class and preferred term.

For the exploratory objective, the serum cortisol, salivary cortisol and salivary cortisone responses at 30 and 60 min after each of the active treatments will be summarised using n, mean, SD, median, minimum and maximum.

A statistical testing hierarchy will be employed to ensure the overall 5% significance level is maintained for primary and secondary outcomes. First, the superiority primary outcomes will both be tested using α=5%. Both must be significant in order to continue; if both are significant, then the non-inferiority and NPA primary outcomes will be tested using a truncated Hochberg procedure to maintain a nominal 5% significance level. If at least one of these meets the criteria for significance, then secondary outcomes for non-inferiority will be tested using Hochberg procedure to maintain a nominal 5% significance (using available alpha after testing the primary objectives).

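### Nasal-dosing symptoms that resolve before 30 min are exempt from AE reporting whatever their severity, so brief local effects leave the AE summary and a brief severe one triggers neither safety rule

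*Protocol article*

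**What the plan says.** Under Safety considerations and AE reporting, the protocol article sets one exemption: "Symptoms associated with the nasal drug administration will not be reported as AEs, unless persistent (defined as still present 30 min after IMP administration". It gives persistence as the sole exception and does not mention severity.

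The same section builds two rules on AEs. For the trial: "The occurrence of one possibly related SAE or two possibly related severe AEs will trigger trial stopping criteria", after which "The trial can only be restarted following discussion with the DMEC and MHRA approval of a substantial amendment". For the participant: "If a possibly related SAE or severe AE occurs in an individual participant, they should not receive any subsequent IMP doses", and the participant is withdrawn.

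Under Final analysis, the safety output is: "AEs, SAEs and SUSARs will be summarised by treatment received, system organ class and preferred term".

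Study aims and objectives makes safety an objective: "The study will collect safety data on the use of Nasacthin in healthy volunteers". The Introduction says of nasal delivery in general that "the side effects of nasal drugs are few, generally attributable to the drug itself rather than the method of delivery, and resolve rapidly".

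Outcomes and assessments adds close observation in the first 30 min, a statement that all AEs are collected and coded, and a non-validated acceptability and tolerability questionnaire at the end of each visit.

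**The concern.** An exemption for trivial, self-limiting discomfort from a nasal spray is ordinary practice. Here it is defined by duration alone, so it also covers a symptom that is intense but short. Because the AE table and both safety rules start from what is reported as an AE, the exemption acts on all three.

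Two things are at stake. The first is description: the intranasal route is what is new about the test, rapidly resolving effects are the kind the Introduction leads one to expect, and these would be missing from the AE table. The second is participant protection: in a crossover, someone with a brief severe local reaction may be due further doses, and the withdrawal rule would not apply. The Study population section allows 20–50% children and names children as the main target group for the test.

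**Working it through.** The plan states no figure on this point, so there is none to reproduce. The check is a reading of the rules, followed by arithmetic on exposure and on the cost of changing the rule.

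**1. The rules side by side**

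| Event after a nasal dose | In AE summary | Counts towards stop | Individual withdrawal |
|---|---|---|---|
| SAE, possibly related | yes | yes (one is enough) | yes |
| Severe, non-serious, possibly related, still present at 30 min | yes | yes (two needed) | yes |
| Severe, non-serious local symptom, gone before 30 min | no | no | no |
| Mild or moderate local symptom, gone before 30 min | no | no | no |

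The third row is the gap. The general statement that all AEs are collected does not close it, because the exemption decides what is reported as an AE. The eligibility re-check at each visit (Study procedures), the allergy and investigator-opinion exclusions (Box 1) and DMEC review (Regulatory approvals and trial oversight) could each prevent a further dose or halt the trial. None of them puts a severity limit on the exemption.

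**2. Exposure covered** (32 completers, four IMPs, two of them nasal)

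- Nasal visits: 32 × 2 = 64 of 32 × 4 = 128, of which 32 are active Nasacthin.
- Only one dose can be last, so each participant has one or two nasal doses followed by another IMP dose: 32 to 64 in total.
- A nasal dose is last in 12 of the 24 possible orders, so the mean is 2 − 0.5 = 1.5 per participant. That gives 32 × 1.5 = 48 if the sequences are balanced (an assumption).

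Repeat visits and dropouts would change these counts.

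**3. What earlier experience can exclude**

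The Introduction reports "a total of 70 doses of Nasacthin have been administered to healthy adult males and children" and describes the product as well tolerated, without symptom counts. Assume that none of the 70 doses gave a brief severe symptom. The one-sided 95% upper bound is 1 − 0.05^(1/70) = 4.19% per dose, and 32 × 0.0419 = 1.34 events in 32 Nasacthin doses. This is a limit on what can be excluded, not an estimate.

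**4. Consequence of counting brief severe symptoms**

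Let p be the assumed rate of brief severe symptoms per nasal dose, with doses independent and active and placebo alike. The chance of reaching the two-event stop is P(X ≥ 2) = 1 − (1 − p)^64 − 64p(1 − p)^63.

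| p | Expected events, 64p | Of these, followed by a later dose, 48p | P(X ≥ 2) in 64 doses |
|---|---|---|---|
| 0.25% | 0.16 | 0.12 | 1.1% |
| 0.5% | 0.32 | 0.24 | 4.1% |
| 1% | 0.64 | 0.48 | 13.5% |
| 2% | 1.28 | 0.96 | 36.7% |

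If only the 32 active doses carry the risk, P(X ≥ 2) is 4.1% at 1% and 13.4% at 2%.

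Over this range, applying the withdrawal rule alone costs about one participant's later visits or fewer. Feeding the same events into the whole-trial stop could halt the study with a probability that is not negligible.

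**The case against.** The strongest objection is that the article condenses Protocol version 1.4, and the full safety section may define severity and add an exception. That stands as the main uncertainty. Even so, the article prints a complete rule with its own definition and a single exception. If a second exception exists, the article misstates the rule, and one look at the full protocol settles it.

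The exempt symptoms may also be meant as those of the act of spraying and not of the drug. On that reading drug effects stay reportable and the gap is smaller. The sentence does not say so and gives staff no way to separate the two in the first 30 min.

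Another objection is that the stopping and withdrawal rules are not mechanical, because calling an event severe or possibly related is itself a judgement. This is right, and it narrows the contrast with the discretionary safeguards. Those rules do, however, prescribe an action once the judgement is made.

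It can also be said that brief discomfort belongs under tolerability, which the questionnaire covers, and that the ethics committee and the MHRA approved the design. This is a fair defence for mild and moderate symptoms. The article does not link the questionnaire to AE coding or to either rule.

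A reader might infer more than the text supports:

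- *Transient symptoms go unrecorded.* The text says only that they are not reported as AEs, and the questionnaire may pick them up.
- *Allergic reactions could be missed.* Hypersensitivity is monitored separately and most naturally lies outside the exemption.
- *The safety comparison is biased.* Nasacthin and nasal placebo fall under one rule. Whether intravenous visits follow a different one depends on the full protocol.
- *Brief severe symptoms must count towards the trial stop.* The last table in the working shows why that is a trade-off and not a plain correction.

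**Conclusion.** The point holds in limited form. As printed, the exemption has no severity limit, so transient local effects of Nasacthin are absent from the AE summary, and a brief severe, non-serious local symptom neither triggers individual withdrawal nor counts towards the stop. No efficacy analysis is affected.

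The size cannot be stated as a number of lost events. The event of most concern is hypothetical: nothing in the article shows that one has occurred, although 70 earlier doses could not rule it out. The rates in the working and the zero count in 70 doses are assumptions. The conclusion also rests on the full protocol containing no severity exception. This is worth considering, with medium confidence.

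**What to change.** First check the full protocol for a severity limit. If there is none:

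- Keep the exemption for mild and moderate administration symptoms that resolve within 30 min.
- Report any severe symptom, and any suspected hypersensitivity reaction, as an AE regardless of duration. Apply the individual withdrawal rule to it where possibly related, and notify the DMEC.
- Leave it to the sponsor and DMEC to decide, and write down, whether brief self-resolving severe symptoms count towards the two-event trial stop. Do not change this automatically.
- Record administration symptoms from 0 to 30 min (type, severity, onset, resolution) on the same form at all visits, and tabulate them by treatment separately from AEs.
- For visits already completed, footnote the AE table with the exemption that applied and show the questionnaire tolerability results beside it.

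The cost is a few eCRF fields, one table, a short wording change, slightly higher reported nasal event counts and an occasional extra withdrawal. Staff already observe participants closely in this window. The main drawback is timing. Recruitment opened on 3 January 2024 with a 12-month window and was on target, so the rule would change part-way through and the AE data would span two rules. If few visits remain, the footnote and the questionnaire results are the parts still worth doing.

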### Dissemination

Trial results will be disseminated in peer-reviewed journals, and in conference presentations at national and international meetings. Authorship will be determined according to the International Committee of Medical Journal Editors guidelines.^18^

### Data availability

Data will not be released without sought permission from the Trial Steering Committee (TSC) before the first publication of primary endpoint analysis.

Final anonymised clinical study datasets and meta-data will be produced and stored in an appropriate format to enable discoverability and sharing. Requests for access to the dataset will be managed via UK Data Service ReSHARE’s established processes and enabled by a Data Sharing Agreement.

### Protocol version

This paper is based on Protocol version 1.4; 12 September 2024.

### Current trial status

The STARLIT-2 study opened to recruitment on 3 January 2024 and has a 12-month recruitment window. Recruitment is currently on target to finish within the specified recruitment period.
